### Randomisation

Subjects are allocated to the sensor or control arm using the web based randomisation service provided by the Clinical Trials Support Unit, University of Nottingham. Randomisation is determined by a computer-generated pseudo-random code using random permuted blocks of randomly varying size, created by the Nottingham Clinical Trials Unit (CTU) in accordance with their standard operating procedure (SOP) and held on a secure server, employing the Stata add-in ralloc [25]. Participants are allocated with equal probability to the sensor or control arm of the study. The randomisations are requested through a PC with internet explorer and internet access. The system is located on a dedicated secure server within the University of Nottingham. All communications between the user's PC and the server are fully encrypted (secured SSL 128 bit encrypted) and via a unique username and password.

### Blinding

In order to mitigate against nurses preferentially giving attention to patients with sensor equipment (i.e. the intervention arm) as compared to those without equipment (i.e. the control arm), we wished to find out if the nurses could be blinded to treatment allocation by the use of "dummy" (inactive) sensor equipment. To test the feasibility of this, we carried out a pilot study conducted over two days, with three 2 hour observation periods each day. Six sensors (4 active and 2 "dummy" sensors) were used with six patients, with one nurse (blinded to the status of the sensors) responding over each 2 hour period. Five nurses were assessed (the fifth nurse on the second day underwent two periods of observations). Four of the five nurses successfully identified the "dummy" versus the active sensors over the observation period. On the basis of this we concluded that it was not feasible to blind nurses to dummy verses active sensor, and therefore we decided not to use dummy sensor equipment with the control arm patients, who will be randomised to standard care alone. Any impact upon the standard care of the control group will be assessed in a qualitative sub study comprising of a non-participant observational study, and in-depth interviews with ward staff.

In order to reduce observer bias, the primary outcome measure is assessed from hospital incident reporting forms by a researcher blinded to treatment group allocation. Secondary outcome participant interviews are conducted away from the bedside so researchers remain unaware of group allocation. In instances where the researcher becomes aware of the intervention the participant has received ("unblinding"), this will be recorded.

A member of the research team, blinded to sensor allocation, enters trial outcome data. To assess the success of blinding, those measuring or entering outcome data are asked to estimate intervention or standard care for each participant, and this will be compared to actual allocation at the end of the study.

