## Background

Falls in hospitals are common, ranging from 3 to 14 for every 1,000 bed days [1]. Over 200,000 falls were reported to the National Patient Safety Agency's (NPSA) National Reporting and Learning System (NRLS) in the 12 months from September 2005 to August 2006, with falls data being reported from 98% of organisations providing in-patient services [2]. In-patient falls result in injury and anxiety to patients and large costs to NHS organisations, including the costs of treating injuries, increased hospital stay, complaints and litigation [3-5].

Elderly in-patients are at particular risk of falling with the incidence of falls being almost triple that for community-dwelling older people [6]. Several factors contribute to this including; age, a history of falling, impaired mobility and special toileting needs. People with dementia are more likely than those without it to require hospital admission, and are at least twice as likely to fall [7-9]. Up to 30% of in-patient falls occur during the first 48 hours of the patients' admission and 75% of in-patient falls occur in the first two weeks of hospital stay [7,10,11].

Our hospital audit data are consistent with published data [2] and has shown that more than half (53%) of all in-patient falls in elderly people in acute care settings occurred at the bedside, during transfers or whilst getting up to go to the toilet. In the majority of cases these falls were unwitnessed. Where patients had been advised to call for assistance they were often reluctant to ask for help as they "did "not want to bother the nurses" or were unable to do so because of cognitive impairment.

Prevention of falls is a priority for NHS policy makers and practitioners. The Healthcare Commission has used falls prevention as a focus for inspecting compliance under patient safety [12]. Despite our increasing knowledge of the aetiology and epidemiology of falls, there is a dearth of evidence for effective falls prevention in hospitals [13-15]. There is good evidence for falls prevention in the community dwelling elderly [16-18], but these findings are unlikely to generalise to the acute hospital setting.

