### Intervention

Those participants randomised to the intervention arm of the trial will receive bedside chair and bed pressure sensors for the duration of their ward admission.

Each sensor device consists of a flexible pressure pad enveloped in thin foam encased in a durable plastic coating such that it confirms to hospital infection control policies. The bed sensor (760 mm × 250 mm × 3 mm) is placed between the bed mattress and the base of the bed in a horizontal position directly under the hip region. The chair sensor (360 mm × 175 mm × 3 mm) is positioned on top of the chair base and/or under a cushion.

The sensors detect pressure changes as the patient rises from the bed or chair, whereafter an alert is sent via radio page to a handheld pager carried by nursing staff. The pager provides the location of the call so staff can respond rapidly and ensure the patient is safe. In this way the sensor system provides an early warning to staff that the patient has left the bed or chair, and may therefore avert a potential fall.

Sensor units are leased from Tunstall Ltd. and are CE marked, complying with the regulatory authorities. Nursing staff on participating will be trained to use the sensors prior to trial recruitment. Members of the research team fit the sensors to the beds and chairs with the sensors left in place until the participant is discharged.

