##### (b) follow up data

Follow up data are collected one day prior or on the day of discharge.

Follow up data includes:

a. Falls, ascertained from hospital incident reporting forms. The use of these incident forms in NUH to record falls is mandatory and enforced by clinical governance processes. Members of the research team collect copies of hospital incident reporting forms from participating wards. Data such as fall event, time, and place, injuries sustained and subsequent actions taken are recorded. Where a medical opinion has been requested, the outcome is recorded, together with any investigations requested. In addition, aggregated, anonymzed data on falls will be collected from hospital incident reporting forms for the trial wards for the 12 month period prior to the trial commencing. The rate of falls in the period prior to the trial commencing will be compared with the control arm rate of falls during the trial to explore whether the use of sensors increases the rate of falls in the control arm.

b. Transfer/mobility and activities of daily living (Barthel ADL). This information is ascertained from the participant or carer, and/or their medical and nursing notes.

c. Quality of life (EuroQol EQ-5D) ascertained by participant interview. Where a participant is unable to participate in an interview, health related quality of life is ascertained from the carer and named nurse.

d. Fear of falling (mFES), ascertained by participant interview. Where a participant is unable to take part in an interview due to poor cognitive ability, this assessment is coded appropriately and excluded from analysis.

e. Mini Mental State Examination (MMSE), through participant interview. The baseline assessment does not account for any acute delirium secondary to the patient's condition on hospitalization, which may improve with treatment. The change in delirium may have an effect on the risk of falling.

f. Length of stay and residential status on discharge, ascertained from medical records.

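### Bedside falls may be detected more often in the sensor arm than in the control arm, and blinded reading of incident forms does not address this

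*Protocol article*

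**What the plan says.** All references are to the protocol article.

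- **Source of the outcome** (follow-up data): "Falls, ascertained from hospital incident reporting forms". No second source of falls is described. On completeness: "The use of these incident forms in NUH to record falls is mandatory and enforced by clinical governance processes". On content: "Data such as fall event, time, and place, injuries sustained and subsequent actions taken are recorded".
- **Blinding**: to reduce observer bias, "the primary outcome measure is assessed from hospital incident reporting forms by a researcher blinded to treatment group allocation". After a pilot with dummy equipment, "we concluded that it was not feasible to blind nurses to dummy verses active sensor", so control patients receive standard care without dummy sensors.
- **Intervention**: when the patient rises, "an alert is sent via radio page to a handheld pager carried by nursing staff", and "The pager provides the location of the call so staff can respond rapidly and ensure the patient is safe". This happens in the sensor arm only.
- **Background**, on bedside and transfer falls in the hospital's own audit: "In the majority of cases these falls were unwitnessed".
- **Outcome measures**: a bedside fall needs no injury. Coming to rest on the floor or a lower level within the curtained area is enough. Injurious falls, at any location, are a secondary outcome.

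**The concern.** The primary outcome counts falls that become known to staff and are written up. The intervention brings staff to the bedside in one arm only, so it may change how many falls become known as well as how many occur. A patient who slips to the floor, gets up unaided and tells no one leaves no trace under usual care. In the sensor arm the same event may be found by a nurse answering the page.

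The blinded reader comes in after this step. Blinded reading can keep decisions about place and injury even-handed for the forms that exist, but it cannot restore a fall for which no form was written.

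If detection differs between arms, the rate ratio mixes prevention with detection. A null result could not then be read simply as an ineffective sensor. The cost-effectiveness analysis inherits the problem, because its effectiveness measure is falls prevented.

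**Working it through.** **1. Do the planned checks cover between-arm detection?**

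| Planned element | What it addresses | Does it compare detection between arms? |
|---|---|---|
| Blinded form reader | Classification of reported falls | No |
| Mandatory incident forms | Reporting of falls that staff know about | No |
| Pre-trial ward rate against control-arm rate | Whether sensors raise the rate of falls in controls | No: usual-care detection on both sides |
| Fidelity observations (two days every 6 months) | Response to alerts | No: control patients generate no alerts |
| Qualitative sub-study | Effect on standard care of controls | No |
| Injurious falls, all locations | A secondary outcome | Only indirectly: not limited to the bedside |

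**2. Reproduce the plan's sample size.** Inputs from Sample size: 8.0 bedside falls per 1,000 bed days and a 19-day stay, so mu = 0.008 x 19 = 0.152 (the article rounds to 0.15); rate ratio RR = 0.65; over-dispersion phi = 1.5; alpha 0.05, taken as two-sided; power 80%. The Signorini formula for Poisson regression with 1:1 allocation gives

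n per arm = phi x [1.96 x 2 + 0.842 x sqrt(2 + 2/RR)]^2 / [2 x mu x (ln RR)^2].

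With ln 0.65 = -0.4308 and sqrt(2 + 2/0.65) = 2.253, this is 900 per arm for mu = 0.152 and 912 for mu = 0.15. The stated 905 lies between them.

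**3. Effect of unequal detection on the rate ratio.** Let u be the share of true falls that are unwitnessed and r the share of unwitnessed control falls never recorded. Suppose every sensor-arm fall is recorded. Then

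observed RR = true RR / (1 - u x r).

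Neither u nor r is in the document, which says only that a majority are unwitnessed. The assumed ranges are u = 0.5-0.7 and r = 0.05-0.20.

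- Low end: 1 - 0.5 x 0.05 = 0.975, so 0.65 becomes 0.667, and 1.00 becomes 1.03.
- High end: 1 - 0.7 x 0.20 = 0.86, so 0.65 becomes 0.756, and 1.00 becomes 1.16.

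**4. Power with 905 per arm, by the formula that reproduces the plan.** The 8.0 per 1,000 comes from ward data, so it is treated as the recorded control rate.

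Power = Phi{ [sqrt(2 x 905 x 0.152 / 1.5) x |ln RR| - 3.92] / sqrt(2 + 2/RR) }, where the square root in the numerator is 13.54.

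| Observed RR | \|ln RR\| | sqrt(2 + 2/RR) | z | Power |
|---|---|---|---|---|
| 0.650 (equal detection) | 0.4308 | 2.253 | 0.85 | 80% |
| 0.667 | 0.4055 | 2.236 | 0.70 | 76% |
| 0.756 | 0.2800 | 2.155 | -0.06 | 48% |

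**5. The opposite direction.** If unblinded staff recorded 10-20% fewer falls in the sensor arm and there were no true effect, the observed rate ratio would be 0.90-0.80. The same formula gives an 11-34% chance of a significant apparent benefit.

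**The case against.** The case against has real force on several points.

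- **Direction and size are not shown.** Nothing in the article compares detection by arm. A reader might infer that falls *are* found more often with sensors and that the bias *must* work against the device. The document supports only a plausible mechanism, and step 5 shows that selective reporting could reverse the sign.
- **Unwitnessed is not undetected.** The audited falls were recorded even though most were unwitnessed. The mechanism needs patients who fall, recover unaided and tell no one, and the article does not say how many there are.
- **Authorship of the forms.** It is natural to infer that unblinded nurses write them, but the article does not name who completes them. The point needs only that a form depends on ward staff learning of the fall.
- **Full recording in the sensor arm is the extreme case.** The fidelity study allows for missed responses and transmitters not re-set.
- **Power can be misattributed.** A Wald test on the log rate ratio gives only 73.5% at 0.65 with no detection bias at all. That gap from 80% is a matter of formula, so the figures above use the formula that reproduces about 905.
- **The Blinding section claims only to reduce observer bias**, the infeasibility of dummy sensors is disclosed, and sensitivity analyses are commonly left to an analysis plan, which is not shown here. Their absence is therefore not the complaint.

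What remains is that the named safeguard for the primary outcome acts after the step at which the arms may differ, and no other described element compares that step between arms.

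**Conclusion.** The point holds as a caution about a possible bias. Falls are counted only from forms that depend on unblinded ward staff learning of them, and the intervention sends those staff to the patient in one arm only. Blinded reading and mandatory forms do not reach that step.

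The likelier concern is better detection with sensors, which would pull the result towards no effect or apparent harm. Under the stated assumptions a true 35% reduction would appear as roughly a 33% to 24% reduction, with power of 76% to 48% in place of 80%. Those figures rest on assumed values of u and r and on complete recording in the sensor arm, so they illustrate sensitivity and do not estimate the bias. Under-reporting in the sensor arm could act the other way. The sample size calculation is not wrong on this account.

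**What to change.** 1. **Pre-specify one sensitivity analysis** of the primary comparison, restricted to injurious bedside falls. Use the article's own definitions of bedside and injurious, and the same over-dispersed Poisson model with length of stay as offset. Place and injury are already taken from the forms. Describe it as less dependent on detection, not free of it: the injury definition includes bruises and abrasions, which can follow a fall that nobody noticed. The cost is fewer events and wider intervals.
2. **Restate the Blinding section**: blinded form reading protects the classification of reported falls, not their detection or reporting.
3. **Commit to reading a null primary result together with the analysis in item 1.**
4. **Where the forms already record how a fall was discovered**, extract this after blinded classification is complete and report it descriptively by arm. The article does not list mode of discovery among the recorded items, so this may not be available.

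Excluding sensor-arm falls found through an alert should not serve as a main sensitivity analysis. It removes events from one arm only, including falls that would have been found anyway. If it is shown at all, label it an extreme bound favouring the sensor.

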### Outcome measures

#### Definition of primary and secondary outcome measures

The primary outcome measure is the number of bedside in-patient falls per 1,000 bed days from time of randomisation until the participant is discharged from the ward.

A bedside fall is defined as an unexpected event in which the participant comes to rest on the ground, floor or lower level in the area around the bedside, with the bedside being defined as the area encompassed by the curtained area surrounding the bed. For participants in side rooms, the bedside is defined as the area of the room.

The secondary outcome measures are:

a. Number of injurious in-patient falls per 1,000 bed days, defined as falls resulting in abrasion, bruise, swelling, cut, laceration, dislocation, fracture or muscle sprain or strain.

b. Length of hospital stay.

c. Residential status on discharge.

d. Transfer/mobility score and activities of daily living, measured using the Barthel Index [26].

e. Fear of falling, measured using the Modified Falls Efficacy Scale (mFES) [27] to ascertain any differential fear of falling in the two participant groups due to an increased awareness of a potential for a fall, or a greater sense of safety arising from sensor use.

f. Health related quality of life, measured using the EUROQOL EQ-5D [28].

g. Participant and staff experience of using bed and chair sensors. This sub-study will be reported separately.

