### Sample size

Based on data obtained from our wards during 2005, we anticipate a rate of bedside falls of 8.0 per 1,000 bed days in the control group, assuming that 53% of all falls occur at the bedside and that the average length of stay is 19 days (mean number of falls per patient = 0.15). To detect a 35% reduction in the rate of bedside falls among the intervention group, assuming 80% power, alpha = 0.05 and an over dispersion parameter of 1.5 (to allow for non-independence of falls within individuals), 905 participants are required in each arm of the trial.

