**Project milestones REFINE**	
2005.	"Bed Sensors Reduce In-patient Falls and Hospital Length of Stay" [32]
2005.	Health and Social Care Technology Award for the Midlands and East
2006.	Planning for a large RCT of inpatient sensors initiated
Dec 2007.	Grant awarded by the Research for Patient Benefit Programme of the National Institute for Health Research, UK (PB-PG-0107-11112)
May 2008.	Ethics approval has been obtained from the Nottingham Research Ethics Committee (reference 07HC006).
Aug 2008.	Study commencement.
Sept 2008.	Ward staff trained, Pilot of equipment and procedures
Oct 2008.	Recruitment commenced
Dec 2010.	Recruitment completed
Feb 2011.	Last participant discharged
April 2011.	Analysis completed
July 2011.	Publication

A Trial Management Group chaired by the principle investigator, comprising investigators, research staff and patient representatives, monitors all aspects of the conduct and progress of the trial, ensures that the protocol is adhered to, and will take appropriate action to safeguard participants and the quality of the trial.

A Trial Steering Committee, comprising the trial management group and three external experts (one of whom acts as chair) has been established to ensure the study governance and conduct complies with good clinical practice guidance.

A sub-group of the trial steering committee, the Data Monitoring and Ethics Committee comprising two of the external members of the steering group (including the steering group chair) and a statistician independent to the study, will receive adverse event forms electronically and will meet as required in the event of an excessive serious adverse event rate or if other information is reported to it which raises concern over the safe conduct of the trial.

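### The closed list that defines an injurious fall leaves out head or intracranial injury, other internal injury and death, so a fall with only such a consequence would be counted as non-injurious

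*Protocol article*

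**What the plan says.** The protocol article, under *Definition of primary and secondary outcome measures*, lists as secondary outcome (a) the "Number of injurious in-patient falls per 1,000 bed days", with injurious falls "defined as falls resulting in abrasion, bruise, swelling, cut, laceration, dislocation, fracture or muscle sprain or strain". It gives no severity grade.

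Two other places bear on the point:

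- *Ascertainment of outcomes, (b) follow up data* describes what is taken from the hospital incident forms: "Data such as fall event, time, and place, injuries sustained and subsequent actions taken are recorded". It adds: "Where a medical opinion has been requested, the outcome is recorded, together with any investigations requested".
- *Project management, governance and administration* (text after Table 2) says that the Data Monitoring and Ethics Committee "will receive adverse event forms electronically and will meet as required in the event of an excessive serious adverse event rate".

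**The concern.** The Background justifies the trial partly by the injury that falls cause and the cost of treating it. Outcome (a) is the only listed outcome that measures injury from a fall, so its definition decides what the trial can report on that question.

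The definition covers surface and musculoskeletal injury only. It is detailed enough to name muscle strain, yet it has no entry for bleeding inside the skull, injury to an internal organ or a death caused by the fall. A researcher who applied it literally to an incident form would have to code a fall with only such a consequence as non-injurious, while coding a fall with a graze as injurious. Few falls are likely to be affected, but they would be among the most important ones. With no severity split, a reader of the result also could not separate fractures from bruises.

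**Working it through.** **Step 1. Is the list closed?** The definition uses *defined as*, followed by named injuries. It contains no *such as*, *including* or *other injury*. The follow-up section, by contrast, introduces its recorded items with *such as*. The outcome definition is therefore closed on its face, while the data collection is not limited to the same list.

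**Step 2. Which falls are missed?**

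| Fall outcome | Counted under (a)? |
|---|---|
| Fracture or dislocation | Yes |
| Head injury with a cut, bruise or swelling recorded | Yes |
| Death, with any listed sign recorded | Yes |
| Intracranial or other internal injury, no listed sign recorded | No |
| Death due to the fall, no listed sign recorded | No |
| Graze only | Yes, with the same weight as a fracture |

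The gap is confined to the fourth and fifth rows.

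**Step 3. The plan's own figures.** *Sample size* states "we anticipate a rate of bedside falls of 8.0 per 1,000 bed days in the control group". The same section puts the bedside share of falls at 53% and the mean stay at 19 days.

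- Bedside falls per control patient: 8.0 × 19 / 1,000 = 0.152. The article states 0.15, so this reproduces.
- Participants per arm, for "To detect a 35% reduction in the rate of bedside falls among the intervention group" with 80% power, alpha 0.05 (two-sided assumed) and overdispersion 1.5, with m the control mean: n = 1.5 × [1.96 × √(2/m) + 0.842 × √(1/m + 1/(0.65m))]² / (ln 0.65)². This gives 900 for m = 0.152 and 912 for m = 0.15. The stated 905 lies between them. It is a calculation for bedside falls, and the definition of an injurious fall does not enter it.

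**Step 4. Falls that outcome (a) draws on.** Outcome (a) covers all in-patient falls, not only those at the bedside.

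- All falls: 8.0 / 0.53 = 15.1 per 1,000 bed days.
- Per control patient: 15.09 × 19 / 1,000 = 0.287.
- Control arm: 905 × 0.2868 = about 260 falls.

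This treats the full 19 days as time at risk, as the plan's own calculation does.

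**Step 5. Size of the effect on outcome (a).** The article gives no injurious share, so the share is an assumption.

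| Assumed injurious share | Control-arm injurious falls | One missed | Two missed |
|---|---|---|---|
| 20% | 0.20 × 260 = 52 | 1.9% | 3.8% |
| 30% | 0.30 × 260 = 78 | 1.3% | 2.6% |
| 40% | 0.40 × 260 = 104 | 1.0% | 1.9% |

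The number missed is also unknown. If 0.5% to 2% of all falls had a serious unlisted injury and no listed sign (an assumption), 260 × 0.005 = 1.3 and 260 × 0.02 = 5.2, or about 1 to 5 falls. Five in 78 would be 6.4%.

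**The case against.** The best case against the point has four parts.

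- **Most serious falls are counted.** Any bruise, swelling, cut or fracture brings a fall into the outcome, and the article does not say how often a serious injury leaves none of these. This stands and keeps the gap small. It does not close it, because whether an intracranial injury counts should not depend on someone noting a mark on the skin.
- **Serious harm is recorded elsewhere.** Injuries sustained are taken from the incident forms without restriction to the list, and adverse event forms go to the monitoring committee. This also stands: nothing serious need be lost to the trial. But a safety channel is not a defined comparison between arms, and the breadth of the raw data does not alter what outcome (a) counts.
- **An any-injury count is a legitimate choice.** It is. Equal weighting is not an error in itself; it is a reason to show severity alongside the count.
- **A severity table is analysis-plan detail.** In part. The table may be planned in a document not shown. The definition, however, is fixed in the article.

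A reader might go further and infer that minor injuries dominate the outcome. The article gives no injury mix, so any such share would be a ratio of assumed rates. The most that can be said is that, without grading, minor injuries could dominate unseen.

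A reader might also infer that injury recording is biased, because ward staff are unblinded. *Blinding* raises preferential attention to sensor patients as a risk to be mitigated, and incident forms are mandatory for falls. No differential recording is shown.

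**Conclusion.** The point holds as a minor flaw in the definition of a secondary outcome. Read as written, secondary outcome (a) would class as non-injurious a fall whose only recorded consequence is head or intracranial injury, other internal injury or death, and it would count an abrasion equally with a fracture.

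The effect on the total injurious-fall rate is probably small: about 1% to 3% for one or two misclassified falls among about 78 in the control arm. That rests on the assumed 30% injurious share and on the assumed number of misclassified falls; neither is in the article. The matter deserves correction because of the kind of event omitted, not because of the number. The primary outcome, the 905 per arm and the power are untouched.

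**What to change.** Extend the definition of an injurious fall with: *head or intracranial injury, other internal injury, any other injury, or death attributed to the fall*. The open term makes the list complete, and the named categories make the coding explicit.

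Tabulate injurious falls by severity and by arm, using the injury, medical-opinion and investigation data that *(b) follow up data* already says are recorded.

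The cost is one amended sentence and one extra table, with no new data collection. There are two limits. First, the serious subset will be small: if 3% to 5% of falls were serious (an assumption), 260 × 0.03 to 260 × 0.05 gives about 8 to 13 in the control arm, so it should be reported descriptively without a test. Second, the medical opinion is available only where one was requested, and that request comes from unblinded ward staff. The table therefore improves the classification but does not make it independent of knowledge of allocation.
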